### Auditing and data management

Each step of the study process, including test conduct, data recording, and data analysis, will be conducted through the guidance of standard operating procedures (SOPs). A research coordinator and the PI will be present at each exercise study to audit and ensure compliance of the test conduct and data recording with SOPs. A linking log will be used to track the recruitment of participants into the study. Participant personal health information (PHI) such as full name, date of birth, MRN, email, and phone number will be collected and stored within the master linking log. All participants will be assigned a study ID (matching their Canadian HPS Program Database ID), which will be used alongside the rest of the results. The linking log will be separately and securely stored on an institutional drive for 5 years post-study closure, after which it will be destroyed. Only designated research personnel will have access to the data. The de-identified dataset will be stored for a period of 7 years after study completion.

### Ancillary and post-trial care

In the unlikely event of research-related side effects or injury, medical care will be provided by the research physician at no charge, and/or the participant will be referred for required medical care. Although no funds have been set aside to compensate the participant in the event of injury or illness related to the study procedures, the participant does not give up any legal rights for compensation by consenting to and participating in this study. The investigator, the hospital, the sponsor, and participants’ agents are not relieved from their legal and professional responsibilities.

### Statistical analysis

Continuous variables will be reported as mean (median) ± standard deviation, and categorical variables will be reported as proportions or percentages. We will employ a repeated measures analysis of variance method with a mixed effects model approach to compare the primary and secondary outcomes between interventions. The model will be adjusted for the period in which the treatment was received to assess for the period effect. An interaction between treatment and period will be included to account for the carryover effect. Relationships between variables and between baseline characteristics and exercise test results will be explored with parametric or non-parametric tests of correlation, as appropriate. The normality of continuous variables will be evaluated using QQ plots and histograms. Model residuals will be assessed graphically to ensure that the model satisfies the normality and constant variance assumptions. The outcome will be log-transformed to stabilize the variable, and possible correlation structures will be employed if the assumptions are found to be violated. We will also test for period and carryover effects. The significance level (*α*) will be set at < 0.05. All analyses will be conducted in the R software, version 4.0.3 [40].

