**Methods:**

We propose a randomized controlled crossover trial in patients with moderate HPS (PaO_2_ < 80 mmHg) and orthodeoxia (supine to upright PaO_2_ decrease > 4 mmHg) comparing the effect of supine vs upright position on exercise. Patients with pulmonary hypertension, FEV1/FVC ratio < 0.65, significant coronary artery disease, disorders preventing or contraindicating use of a cycle ergometer, and/or moderate or severe ascites will be excluded. Participants will be randomized to cycle ergometry in either the supine or upright position. After a short washout period (a minimum of 1 day to a maximum of 4 weeks), participants will crossover and perform an exercise in the alternate position. Exercise will be performed at a constant work rate of 70–85% of the predicted peak work rate until the “stopping time” is reached, defined by exhaustion, profound desaturation, or safety concerns (drop in systolic blood pressure or life-threatening arrhythmia). The primary outcome will be the difference in the stopping time between exercise positions, compared with a repeated measures analysis of variance method with a mixed effects model approach. The model will be adjusted for period effects. *P* < 0.05 will be considered statistically significant.

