^†^Univariate analyses are presented for each variable, continuous variables assessed with a 2-sample *t*-test, and categorical variables with a chi-squared test. Variables were assessed on the same day as orthodeoxia or within an interval of ≤ 1 year

To our knowledge, this is by far the largest analysis of both the prevalence and risk factors for orthodeoxia in HPS. Given that patients with orthodeoxia had more severe hypoxemia, it was not surprising that our more “severe” HPS cohort (compared to other reports) had a high observed orthodeoxia prevalence of 66.1% (Table 3). We complimented this with an analysis of our current active HPS database, revealing that six patients currently meet the inclusion criteria. Additionally, a review of referrals in the last 3 years reveals that an average of 4 eligible patients is referred to our program each year. Based on a recruitment target of 50%, this analysis of the Canadian HPS Program Database suggests that we will be able to recruit 10 eligible participants to this study in the 4-year recruitment window allowed by study funding. We believe that this target is achievable, particularly with our pessimistic 50% recruitment target, since patients with HPS and orthodeoxia have no effective treatment options other than liver transplant, the study involves nearly no risk, and the study offers an opportunity to identify a clinically beneficial exercise strategy for the individual.

A crossover design has previously been successfully employed in patients with HPS [30]. The advantage of the crossover design in rare diseases such as HPS is that each participant will undergo both interventions, and within-person comparisons will limit confounding and reduce inter-subject variability, thereby reducing the sample size required to demonstrate an effect [38]. The crossover design is well-suited to an exercise intervention because there is no anticipated therapeutic carryover effect, obviating the need for a washout (we allowed for a 1-day minimum “washout” period for recovery from the prior exercise test). We established a 4-week maximum period between tests to minimize any possible period effect (i.e., to prevent significant disease progression by the time of the second test). The possibility of a period effect due to familiarity with the cycling exercise will be evaluated statistically.

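### The treatment-by-period interaction in the primary crossover model cannot adjust the position effect for carryover without reducing it to a first-period comparison between different people

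*Protocol article*

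**What the plan says.** The Statistical analysis section plans a repeated-measures "mixed effects model approach to compare the primary and secondary outcomes between interventions". Period enters as a main effect: "The model will be adjusted for the period in which the treatment was received to assess for the period effect". The next sentence adds, without any condition, "An interaction between treatment and period will be included to account for the carryover effect". Later in the same section comes "We will also test for period and carryover effects", with no rule for what follows from the result. The software is fixed ("All analyses will be conducted in the R software, version 4.0.3"), but the factor coding and the contrast that yields the position effect are not given.

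Two other places bear on this. Recruitment and power justifies the crossover by its within-person comparison in a rare disease, sets the target at 10 participants, and says of this type of intervention that "there is no anticipated therapeutic carryover effect, obviating the need for a washout". The Methods part of the abstract describes the primary model with period only: "The model will be adjusted for period effects".

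**The concern.** Each participant is tested once supine and once upright, in one of two orders. Such data have four cell means (two sequences by two periods). Position, period and an intercept use three of them. The one remaining degree of freedom is the difference between the two sequence groups. That single contrast is at once the sequence effect, the treatment-by-period interaction and the differential carryover. It is a comparison between people, and the data cannot separate its three meanings.

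Correcting the position effect for it therefore removes the second period from the estimate. The trial can aim at 10 participants only because each serves as their own control, so a primary estimate that drops this comparison would give up the reason for the design. The sentence is also attached to the primary outcome, so it bears on which quantity the main test estimates.

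**Working it through.** **Inputs.** From the protocol: two orders of testing (Trial design); 10 participants (Recruitment and power); position, period and their interaction in the model, analysed in R (Statistical analysis). Assumed, because the protocol gives neither: an equal split (5 per sequence), and the within-person correlation rho. The per-period SD is written s; it cancels from the ratios. The protocol gives no figure for the effect of the interaction, so there is none to reproduce.

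**Step 1: what each quantity estimates.** Let m be the upright mean in period 1, t the position effect (supine minus upright), p the period effect, and cS and cU the carryover into period 2 after supine and after upright.

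| Sequence | Period 1 | Period 2 |
|---|---|---|
| Supine first | m + t | m + p + cS |
| Upright first | m | m + p + t + cU |

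- Period-1 contrast: (m + t) - m = t. It is free of carryover but compares different people. With 0/1 coding and period 1 as reference, this is the position coefficient once the interaction is in the model.
- Period-averaged, within-person contrast: half of [(supine-first: period 1 minus period 2) + (upright-first: period 2 minus period 1)] = half of [(t - p - cS) + (t + p + cU)] = t + (cU - cS)/2. It keeps the crossover's precision but still contains half of any differential carryover.
- Interaction: upright-first total minus supine-first total = cU - cS. This is a between-person contrast of the sequences.

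So the only carryover-free estimate of t is the period-1 contrast.

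**Step 2: precision, 5 per sequence.**

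- Period-1 variance: s²/5 + s²/5 = 2s²/5.
- Within-person variance: (1/4) × 2 × [2s²(1-rho)/5] = 2s²(1-rho)/10.
- Variance ratio: 2/(1-rho). SE ratio: sqrt(2/(1-rho)).

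Both contrasts have 8 degrees of freedom. The last column is the power of the period-1 contrast at the effect for which the within-person contrast has 80% power (noncentral t).

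| rho (assumed) | Variance ratio | SE ratio | Period-1 power |
|---|---|---|---|
| 0 | 2.0 | 1.4 | 51% |
| 0.5 | 4.0 | 2.0 | 29% |
| 0.7 | 6.7 | 2.6 | 20% |
| 0.9 | 20 | 4.5 | 10% |

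**Step 3: check by fitting the models.** In 200 simulated trials (5 per sequence, per-period SD 11.5 min, rho 0.8 assumed) a random-intercept model was fitted in three ways.

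| Model | Mean SE of position effect |
|---|---|
| Position + period | 2.33 min |
| With interaction, 0/1 coding | 7.00 min |
| With interaction, sum-to-zero coding | 2.33 min |

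The 0/1-coded coefficient equalled the period-1 mean difference to about 1e-13. The sum-to-zero estimate equalled the estimate without the interaction. The formulas give 11.5 × sqrt(2/5) = 7.27 and 11.5 × sqrt(2 × 0.2/10) = 2.30 min, in line with the fits.

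**Step 4: an unequal split.** In one simulated data set with 4 and 6 per sequence (SD 3, rho 0.8, variances treated as known), the period-averaged estimate and SE were again the same with and without the interaction (2.363, SE 0.612).

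**The case against.** The strongest reply is that the plan describes an analysis of variance, and an ANOVA tests the position main effect, not a single 0/1-coded coefficient. This is correct and it limits the point. In a simulated data set with 5 per sequence (SD 3, rho 0.8), the sequential ANOVA test of position was the same with and without the interaction (chi-square 7.907 in both), and so was the period-averaged estimate (1.687, SE 0.600). Only the raw coefficient lost precision (SE 1.90). With 4 and 6 per sequence, the sequential test was unchanged when period was entered first and somewhat smaller when position was entered first (12.56 against 14.89). A reader might infer that using R by itself produces the loss; the protocol does not support that.

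A second reply is that coding and contrasts belong in an analysis plan that is not shown. Their absence is indeed no fault. But the protocol states both the term and its purpose, and an analysis plan could only choose between the two outcomes in the working. Neither adjusts for carryover while keeping the within-person comparison.

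Three further inferences are tempting and should be resisted:

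- That a two-stage procedure is planned, in which a carryover test decides whether period 2 is used. The protocol announces a test but no decision rule.
- That checking for carryover contradicts not expecting it, or that the abstract contradicts the main text. A check can accompany an expectation, and an abstract condenses.
- That the loss can be sized from the plan's detectable difference of 2.85 min by solving for the correlation that reconciles it with an SD of 11.5 min. The protocol calls 11.5 the SD of the change, and with 10 participants it gives 2.80 × 11.5/sqrt(10) = 10.2 min, not 2.85. A correlation solved from that pair would reflect this separate discrepancy and is not a plan input.

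**Conclusion.** The point holds in conditional form. As stated, the interaction either fails in its purpose or costs the precision that the crossover was chosen for; which of the two depends on how the position effect is extracted. The aliasing follows from the two-by-two design and needs no assumption about variability.

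Under the costly reading, the loss is at least a factor of 1.4 in standard error for any rho of 0 or more, and 2.0 to 4.5 for rho between 0.5 and 0.9. These figures rest on equal sequences, equal variance in both periods, both tests completed by all 10 participants, and an assumed rho. Under the period-averaged reading the loss is nil. The harm is therefore possible, not certain, but the wording about accounting for carryover points towards the costly reading, and the primary result should not hang on that choice.

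**What to change.** Remove the interaction from the primary model. State that the position effect, with its 95% confidence interval and small-sample degrees of freedom, comes from a model with position and period as fixed effects and participant as a random effect. Use the same model for the secondary outcomes compared in this way.

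Rely on the design for carryover, as Recruitment and power already argues (at least one day between tests, none anticipated). If a carryover or sequence comparison is still wanted, report it descriptively or as a sensitivity analysis, and say that it neither chooses nor alters the primary estimate.

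The cost is a change to one sentence and a qualifying clause on the carryover test. It needs no new data and less analysis, and it brings the main text into line with the model in the abstract.

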## Discussion

Our study aims to investigate the effect of position change on exercise capacity in HPS patients with orthodeoxia. This will be the first study to describe exercise capacity in the supine position in HPS, the first to compare with upright exercise, and the first to describe the use of a CWRET protocol in a cohort with this disease. Given the novelty of our research question and approach, the development of this study posed a number of unique challenges and opportunities which merit discussion.

### Study population and design

We chose to include patients with at least moderate HPS (PaO_2_ < 80 mmHg), in order to ensure that the degree of observed orthodeoxia is both clinically and physiologically significant. Tissue oxygen delivery (DO_2_), which is the physiologic substrate for the hypothesized position-related changes in exercise capacity that we seek to demonstrate, is dependent on oxygen saturation, which is in turn correlated with PaO_2_ through the sigmoidal oxyhemoglobin dissociation curve. Given the flat shape of this curve at higher PaO_2_ levels, changes in PaO_2_ of just over 4 mmHg (the definition of orthodeoxia) would not result in any significant changes in oxygen saturation in patients with a baseline PaO2 ≥ 80 mmHg.

Our use of a CWRET protocol is novel in this population, as prior studies of exercise testing in HPS (Table 1) have almost exclusively employed incremental exercise protocols [7–9, 12]. Given the severe baseline disease in our expected patient population (Table 3), with a predicted mean PaO_2_ drop of 20 mmHg at peak exercise [7], we believe that an incremental exercise protocol would result in profound desaturation requiring cessation for safety reasons, with a high resulting likelihood of a submaximal test. Accordingly, the main variable of interest in an incremental exercise protocol, VO_2peak_, would not likely be achieved in most participants. To address this, we chose a high-intensity CWRET, which has been widely used to assess the changes in exercise tolerance following interventions in other chronic hypoxemic lung diseases [26].

The constant work rate in a CWRET is typically set at 70–85% of the peak work rate measured on incremental exercise testing (IET) [26]. Given that an IET was not feasible in our population, we instead adopted a validated prediction equation for estimating peak work rate based on 6-min walk distance (6MWD) in patients with COPD [27, 41]. Given that peak work rate is affected by ventilatory impairment and dynamic hyperinflation in COPD, neither of which appears to play a role in HPS, this represents a vulnerability in our testing protocol.

### Safety

The primary outcome in our study is stopping time, as determined by either reaching tLIM or experiencing desaturation to our pre-set safety stopping criterion, which is the lower of 80% or the nadir desaturation seen on room air 6MWT. There have been no reports of adverse events while performing CWRET [26]. While there is no definitive threshold at which arterial desaturation becomes hazardous [26], cardiopulmonary exercise testing (CPET) guidelines from the American Thoracic Society and American College of Chest Physicians suggest a saturation of ≤ 80% (with accompanying signs and symptoms of severe hypoxemia) as one of the indications for exercise termination [42, 43]. However, patients with HPS are well adapted to hypoxemia [1]. These patients often present after a prolonged period of undiagnosed hypoxemia and are encouraged to exercise to preserve muscle mass despite significant exercise desaturation (which occurs even with oxygen supplementation) [44, 45]. Furthermore, many patients who require oxygen do not use it at all times [46]. Accordingly, and because many patients in our severe population would desaturate to 80% at rest or with minimal exertion while upright, we added an individualized stopping criterion set at the nadir desaturation experienced on room air 6MWT. This novel approach will enable patients with severe disease to perform a sufficient amount of exercise for positional differences to be detectable and given that it likely reflects a level of desaturation that patients typically experience in their daily lives, and will maintain a reasonable margin of safety.

### Clinical relevance of the potential results

Exercise has been shown to have numerous health benefits, ranging from reducing the risk of heart disease, stroke, osteoporosis, diabetes, and cancer to improving mental health [47]. Unfortunately, patients with HPS are unable to realize the short- or long-term (training) benefits of exercise due to severe exercise limitations caused by hypoxemia. If our hypothesis proves correct, a supine exercise protocol would empower these patients to exercise for longer periods of time. Furthermore, supine exercise could enable a more effective long-term exercise training program. Exercise training results in improvements in exercise capacity, including maximum oxygen uptake (VO_2max_), VO_2peak_, and muscle mass in patients with cirrhosis [4, 48, 49]. This could be particularly impactful for patients with HPS awaiting liver transplant, given that this is the only treatment for HPS, and that pre-transplant exercise capacity predicts post-transplant survival [50, 51]. Every 100-m increase in baseline 6MWD is associated with a 52% reduction in 1-year post-transplant mortality [52], and preoperative exercise capacity independently predicts respiratory complications post-liver transplant [53]. Furthermore, the median liver transplant wait time in severe HPS is 200 days [54], and these patients experience progressive hypoxemia [3, 44], resulting in worsening exercise limitation while awaiting transplant. It is also of note that the HPS patients being targeted by this intervention—those with orthodeoxia—tend to have a lower baseline PaO_2_ and are thus more likely to require a liver transplant for HPS.

If positive, this study will establish the efficacy of supine exercise in this population, enabling this to become a routine part of HPS management, including in non-transplant and pre-transplant settings. This evidence would be required to justify the cost and complexity of a supine exercise prescription. Our results would warrant future studies investigating the long-term physiologic and clinical benefits of a supine exercise training program in HPS, including effects on patient-relevant outcomes such as quality of life, dyspnea, and liver transplant outcomes. Our data suggest that two-thirds of patients with at least moderate HPS have orthodeoxia, representing a significant population of patients (particularly, those with the most severe disease) that could stand to benefit. We also believe that findings from our unique exercise protocol will advance understanding of the physiology of this disease and lay the foundations for larger future studies.

### Limitations

It is important to note that our findings will only be applicable to patients with HPS who have orthodeoxia. As noted, 66% of patients with at least moderate HPS had orthodeoxia in our cohort, but smaller studies have reported an orthodeoxia prevalence as low as 14% [34] in all-comers with HPS, and this requires further study. We also note that while orthodeoxia is measured in the supine vs the standing position, the upright bicycle exercise protocol more closely simulates sitting than standing, and prior reports have suggested that orthodeoxia is less pronounced in the sitting compared to the standing position [55]. A smaller positional change in PaO_2_ could reduce the predicted effect of position on exercise capacity.

## Trial status

Protocol version #3, version date 27 August 2019. Enrollment into the trial has started and is expected to be finalized by approximately July 1, 2023.

## Data Availability

The datasets generated and/or analyzed during the current study will be made available by the corresponding author to fellow investigators, upon reasonable request and after approval by the institutional research ethics board. There are no contractual relationships limiting anonymous data sharing.

## Abbreviations

HPS: Hepatopulmonary syndrome
VO_2peak_: Peak oxygen consumption
IPVDs: Intrapulmonary vascular dilatations
PaO_2_: Partial pressure of arterial oxygen
COPD: Chronic obstructive pulmonary disease
FEV1/FVC: Forced expiratory volume in 1 s over forced vital capacity
AaDO2: Alveolar-arterial oxygen gradient
AO_2_: Partial pressure of alveolar oxygen
*P*_atm_: Atmosphere pressure
*P*_H2O_: Water vapor partial pressure
PaCO_2_: Arterial carbon dioxide pressure
CWRET: Constant work rate exercise test
6MWT: Six-minute walk test
RPM: Revolutions per minute
tLIM: Tolerable limit
VO_2_: Oxygen uptake
VE: Minute ventilation
HR: Heart rate
SpO_2_: Arterial oxygen saturation
VCO_2_: Carbon dioxide production
*VE*_max_: Maximum minute ventilation
AT: Anaerobic threshold
DLCO: Diffusion lung capacity of carbon monoxide
MELD: Model for end-stage liver disease score
MAA: Macroaggregated albumin
FiO_2_: Fraction of inspired oxygen
6MWD: Six-minute walk distance
SD: Standard deviation
MCID: Minimal clinically important difference
DO_2_: Tissue oxygen delivery
IET: Incremental exercise testing
CPET: Cardiopulmonary exercise testing
VO_2max_: Maximum oxygen uptake
